### Safety and adverse events

MS has a good safety profile, with no reported adverse effects [37]. Nevertheless, all adverse events, which include (but are not limited to) any unexpected signs and symptoms, newly diagnosed disease, unusual laboratory findings or hospitalizations, will be documented, regardless of whether the adverse event is related to MS. In cases where there is deterioration in a subject’s preexisting disease during the course of the study, this information will also be documented as an adverse event. During every follow-up visit, subjects will be asked if they are experiencing any adverse effects.

### Randomization

Subjects will be assigned in a 1:1 allocation to either the active or sham MS group using computer-generated, permuted block randomization, with variable block sizes of four, six and eight, by an independent pharmacist with no clinical involvement in the trial. Details of the allocated group are given in sequentially numbered, opaque, sealed envelopes to an appointed nurse involved in administering the treatments to subjects. The independent pharmacist who generates the randomization list will ensure that the envelopes are opaque and impermeable when held to the light. Additionally, the sealed envelopes are stored in a locked cabinet accessible only by the appointed nurse. Enrollment of subjects (assessment of eligibility, discussion of the trial, obtaining informed consent) will be done by investigators and clinicians who are blinded to treatment allocation. Following enrollment of a subject, the investigator will assign the subject a unique identification number. In the first treatment session for each subject, the appointed study nurses will sequentially open the envelopes. The subject’s unique identification number and date will be written on the appropriate allocated envelope.

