**Methods/Design:**

One hundred twenty subjects with stress urinary incontinence will be randomized in a 1:1 allocation to either active or sham magnetic stimulation using computer-generated, permuted blocks of variable sizes. Subjects will receive 2 sessions of magnetic stimulation per week for 8 weeks (16 sessions total). The primary outcome is the improvement in severity of involuntary urine loss based on the International Consultation on Incontinence Questionnaire for Urinary Incontinence Short Form at the end of treatment sessions compared with baseline. Secondary outcomes include cure, stress urinary incontinence–related symptoms (incontinence episode frequency, urine loss in 1-hour pad test, pelvic floor muscle strength) and health-related quality of life (Patient Global Impression of Improvement, International Consultation on Incontinence Questionnaire–Lower Urinary Tract Symptoms Quality of Life and EQ-5D). The safety of magnetic stimulation will also be assessed. Besides evaluation of clinical treatment effectiveness, cost-effectiveness analysis using patient-reported outcomes will be performed.

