### Blinding and unblinding and control for bias

Investigators who carry out outcome measure assessments and statisticians who perform data analysis will not be informed of the allocation assignment. The same appointed study nurses who sequentially open the treatment allocation envelopes will be in charge of administering treatments for the subjects during each visit, and they will not be involved in any outcome assessments. Formal training on operating the QRS-1010 PelviCenter will be provided to the study nurses by an engineer from QRS International. Additionally, treatment appointments will be handled by the independent study nurses, and the investigators will not come into contact with the subjects at any time during the treatment sessions. All personnel involved in the study will adhere to standard operating procedures, with clear separation between investigators who conduct outcome assessments and study nurses who administer the treatments.

In the event of an unexpected medical emergency, subject allocation may be unblinded to the investigator or clinician. The investigator will report the unblinding to the sponsor, followed by submission of a detailed report to the sponsor. The events in which unblinding may occur include (but are not limited to) (1) the subject becomes pregnant while receiving the intervention; (2) an adverse event requires unblinding to provide safety information necessary to manage the subject’s condition; and (3) a serious adverse event requires unblinding to decide whether to continue or discontinue participation. An unblinding report will be completed by the investigator, with reasons for the unblinding specified.

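### Envelopes are used in order of first session, and the unblinded nurses who hold them also handle appointments, so concealment is incomplete: an opportunity for selection bias, not evidence of it

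*Protocol article*

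**What the plan says.** The Randomization section describes a 1:1 list using "permuted block randomization, with variable block sizes of four, six and eight". The list is prepared by an independent pharmacist and supplied in numbered, sealed, opaque envelopes. On custody it says that "the sealed envelopes are stored in a locked cabinet accessible only by the appointed nurse". On timing it says: "In the first treatment session for each subject, the appointed study nurses will sequentially open the envelopes". The investigator gives each enrolled woman a unique identification number, and then: "The subject’s unique identification number and date will be written on the appropriate allocated envelope". Enrolment itself "will be done by investigators and clinicians who are blinded to treatment allocation".

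The section on blinding and control for bias adds two facts: "The same appointed study nurses who sequentially open the treatment allocation envelopes will be in charge of administering treatments" and "treatment appointments will be handled by the independent study nurses". It also lists safeguards. The treating nurses neither enrol nor assess, a second nurse counterchecks the opening of envelopes, and baseline characteristics are compared between groups.

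Table 1 (Study design) places consent and eligibility at visit 0, week 0, and randomization at visit 1, week 1. Trial status reports that recruitment is complete.

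**The concern.** Concealment has to hold until a particular woman is tied to a particular assignment. Here the blinded investigator controls who enters the trial, but the tie is made later, at the first session, by staff who know what earlier women received. If two or more enrolled women are waiting, the order in which they are booked decides who takes the next envelope.

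If booking were influenced by a guess about the next arm, the groups could differ in prognosis at the moment of assignment. That would carry into the week-8 comparison of ICIQ-UI-SF responders. Blinded outcome assessment would not repair it, because the groups would already differ before treatment.

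**Working it through.** **Step 1: who controls what, from the text**

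| Link | Who or when | Where |
|---|---|---|
| Entry into the trial | Blinded investigators and clinicians, visit 0 | Randomization; Table 1 |
| Custody of envelopes | Appointed nurse only | Randomization |
| Use of the next envelope | In sequence, at each first session, visit 1 | Randomization; Table 1 |
| Knowledge of past arms | Nurses who open envelopes also treat | Blinding and unblinding |
| Treatment appointments | Study nurses; first session not excepted | Blinding and unblinding |
| Order of women along the list | No rule given | – |

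The countercheck by a second nurse concerns the envelopes and the assignments made from them, not the order of the women. The bar on enrolling and assessing does not reach booking. The baseline comparison may detect a measured difference afterwards but prevents nothing, and it cannot see unmeasured traits such as motivation.

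**Step 2: how predictable is the next envelope?**

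The plan states no figure to reproduce. Inputs: block sizes 4, 6 and 8 (Randomization) and 120 women ("One hundred twenty subjects with stress urinary incontinence will be randomized in a 1:1 allocation"). Assumptions not in the document: the three sizes are equally likely, there is one unstratified list, and one guesser knows all past allocations and the set of sizes but not the size of each block.

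A guesser who always names the arm that is behind, and tosses a coin when the arms are level, makes the following expected number of correct guesses in a complete block of size 2b:

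b + (2^(2b) / C(2b, b) − 1) / 2

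- Size 4 (b = 2): 2 + (16/6 − 1)/2 = 2.83, or 71%
- Size 6 (b = 3): 3 + (64/20 − 1)/2 = 4.10, or 68%
- Size 8 (b = 4): 4 + (256/70 − 1)/2 = 5.33, or 67%

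With equally likely sizes: (2.83 + 4.10 + 5.33) / (4 + 6 + 8) = 12.26/18 = 68%. Over 120 assignments that is 0.681 × 120 ≈ 82 correct guesses, against 60 by chance. Block size need not be known, because the imbalance returns to zero at the end of every block.

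**Step 3: check by simulation**

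A simulation of 3,000 lists of 120, with a guesser who updates the probability of each possible block size, gave:

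- best guess correct: 67.9%
- next arm certain: 2.25% (about 3 of 120)
- next arm predictable with probability of at least 75%: 34.3% (about 41 of 120)

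The same simulation with fixed blocks gave certainty for 33% (size 4), 25% (size 6) and 20% (size 8) of assignments. Varying the block size therefore removes nearly all certainty but leaves the better-than-chance guess almost unchanged.

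**The case against.** The strongest reply is that several steps needed for harm are not in the document.

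- **Linkage.** The article does not say when the identification number is written on the envelope, and its wording is compatible with an envelope already designated for the woman. Operating procedures that are not shown may settle this. That is fair as to the moment of writing. It does not remove what is stated: envelopes are taken in sequence at first sessions, and no rule ties that sequence to enrolment.
- **Booking.** The sentence on appointments appears where the article explains how investigators are kept away from treatment. It does not say that nurses choose who starts first or that several women wait at once. It also assigns appointments to the nurses without exception. Reading the independent study nurses as the treating nurses is an inference, supported by the Discussion, where independent study nurses coordinate treatment.
- **Knowledge.** Six hospitals are named. With separate lists or nurses, each nurse would know less.
- **Prognosis.** Baseline severity is recorded at visit 0, and no passage gives it to the nurses. A specific route such as sending milder women to active stimulation is therefore not shown.

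A reader might infer that the nurses could choose each woman's arm, or that allocation was steered. The document supports neither. The next envelope is sealed, its content is nearly always uncertain, and nothing indicates that anyone acted on a guess.

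**Conclusion.** The point holds as a weakness of procedure. As written, assignment follows the order of first sessions, unblinded staff hold both the envelopes and the appointments, and no stated safeguard controls which enrolled woman comes next.

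The 68% guess rate is a ceiling. It rests on equally likely block sizes, a single list and one nurse or team that tracks every allocation. It measures predictability and is not a bias. Turning it into bias would also need more than one woman waiting, some knowledge of prognosis and a willingness to use both. The document gives no basis for putting a figure on the effect on the week-8 responder difference, and none is offered here.

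**What to change.** **Procedure.** The blinded investigator issues consecutive numbers at enrolment, and that number is the envelope number. The envelope stays sealed until the first session. A woman who leaves before opening counts as not randomized and her sealed envelope is set aside. Randomization then still takes place at visit 1. The replacement rule under Subject withdrawal, and the rule under Statistical analysis that counts later withdrawals as failures, still apply. The cost is a change of wording with the same envelopes and staff. A set-aside envelope can leave its block slightly unbalanced.

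**This trial.** Recruitment is complete, so the procedure can no longer change any assignment. What can still be done:

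1. Compare enrolment order with envelope order, using the recorded numbers and dates. Take enrolment order from the consent date, because the identification number is described only as unique, not as consecutive.
2. Report the number of out-of-order assignments by arm, with the baseline severity of those women.
3. If the primary outcome is also analyzed without them, label it a sensitivity analysis and keep the intention-to-treat comparison of all randomized women as primary. Ordinary scheduling also produces out-of-order starts, so such a start is not a sign of steering in itself.

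The check relies on records the trial should already hold and needs no new data collection. Consistent orders would largely close the question. Frequent departures, or departures that differ in severity between arms, should be disclosed with the result.

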### Blinding and unblinding and control for bias

Investigators who carry out outcome measure assessments and statisticians who perform data analysis will not be informed of the allocation assignment. The same appointed study nurses who sequentially open the treatment allocation envelopes will be in charge of administering treatments for the subjects during each visit, and they will not be involved in any outcome assessments. Formal training on operating the QRS-1010 PelviCenter will be provided to the study nurses by an engineer from QRS International. Additionally, treatment appointments will be handled by the independent study nurses, and the investigators will not come into contact with the subjects at any time during the treatment sessions. All personnel involved in the study will adhere to standard operating procedures, with clear separation between investigators who conduct outcome assessments and study nurses who administer the treatments.

In the event of an unexpected medical emergency, subject allocation may be unblinded to the investigator or clinician. The investigator will report the unblinding to the sponsor, followed by submission of a detailed report to the sponsor. The events in which unblinding may occur include (but are not limited to) (1) the subject becomes pregnant while receiving the intervention; (2) an adverse event requires unblinding to provide safety information necessary to manage the subject’s condition; and (3) a serious adverse event requires unblinding to decide whether to continue or discontinue participation. An unblinding report will be completed by the investigator, with reasons for the unblinding specified.

Various measures will be taken to control for sources of bias. For selection bias, differences between the baseline characteristics of the two treatment groups will be compared to ensure that randomization is accomplished successfully. The appointed study nurse will sequentially open the envelopes, which will be counterchecked by another study nurse to ensure correct implementation of treatment assignments. To avoid performance and detection bias, the investigators are not allowed to be present in the treatment room. The appointed nurses who administer treatment will not be involved in enrolling the patients or in any outcome measure assessments. To evaluate the effectiveness of blinding of study participants, each subject will be asked to answer the following question at the end of the 16 treatment sessions: Which treatment do you think you received? The subject will have three possible answers: “active treatment”, “don’t know” or “sham treatment”. Patients’ ability to correctly identify treatment assignment at the end of the 8-week treatment will be analyzed and compared between the two treatment groups. Finally, to control for attrition bias, differences between the number of withdrawals from the study, including the reasons for withdrawal, will be analyzed and compared between the two treatment groups.

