### Statistical methods

#### Sample size calculation

Two types of sample size calculations were performed: non-repeated measures and repeated measures. Our primary outcome of interest is the difference in proportion of responders between the active and sham groups after 8 weeks of treatment, defined as a reduction of 5 points or more from baseline to 8 weeks in the ICIQ-UI-SF total score. On the basis of outcomes derived from previously published data on MS, it is anticipated that MS will improve symptoms in 60 % (p1 = 0.6) of subjects with SUI, whereas sham MS will improve symptoms in 30 % (p2 = 0.3) of subjects with SUI [11, 13]. Thus, a minimum sample size of 88 (44 per arm) is powered to detect a difference of at least 30 % (δ = 0.3), with a 95 % confidence interval (α = 0.05) and statistical power of 80 % (β = 0.2) [38]. Allowing for a 25 % dropout rate, the enrollment goal is 120 subjects.

We also calculated our sample size using PASS^13^ Sample Size Software (NCSS Statistical Software, Kaysville, UT, USA) [39]. The tests for two proportions in a repeated-measures design, which can be used to calculate sample size in a mixed-model analysis of repeated measures data, was selected from among the PASS^13^ statistical tools. Using the same parameters (δ = 0.3, α = 0.05 and β = 0.2), an autoregressive AR(1) covariance pattern with autocorrelation of 1.0, and a design with six repeated measurements, a total sample size of 84 (*n* = 42 in each arm) was obtained. As the sample size calculated using a test of simple differences in proportion was higher, we selected the initial calculated sample size.

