## Discussion

Our trial is a prospective, randomized, double-blind, sham-controlled trial of SUI using pulsed MS. The trial is adequately powered and will use validated outcomes. Previous studies conducted with MS had inherent flaws, resulting in inconclusive evidence on this treatment modality. A search of trial registers indicates that there are currently no ongoing, prospective clinical trials investigating our research question of interest (last search done on 5 December 2014).

There is a need for a high-quality randomized clinical trial on this topic with a sham group, adequate sample size, appropriate methodology and validated outcome measures, as well as long-term follow-up [19]. We intend to address the shortcomings of previous studies in our trial and to obtain convincing evidence on the efficacy of MS. We acknowledge the importance of applying a sham MS as a control. We will use a specially designed MS device for the purposes of this trial. The appearance and noise are identical to the active treatment. The sum of energy output of the 8-week sham treatment is lower than the sum of energy output of one 20-minute active mode run ([name], personal communication). Furthermore, we will recruit only subjects who are naive to MS. All subjects will be told that they may experience a tingling sensation. Subjects will also be assessed for effectiveness of blinding at the end of the 8-week treatments. To further allow for double-blinding, all assessors involved in the study will be deliberately prohibited from entering the treatment room, and treatment will be coordinated by independent study nurses. Collectively, these measures allow better blinding of subjects with the aim to diminish the placebo effects.

Next, we determined our sample size based on a priori calculation to ensure that our study is adequately powered to answer our primary outcome of interest. To evaluate the effects of MS on SUI, we selected various subjective and objective outcome measures as recommended by international guidelines [44, 45]. Further, we chose a patient-reported outcome, the ICIQ-UI-SF questionnaire, as our primary outcome measure because we recognize the importance of judging treatment benefit from a patient’s perspective [24]. We hope that use of standardized, internationally accepted tools will ease data pooling in meta-analyses, limiting the number of high-quality clinical trials required to draw concrete conclusion on this treatment option.

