MS is a non-invasive procedure and has been shown to be effective in SUI in various open-label studies [23]. Further advantages are no reported adverse events, unnecessary to undress, automatic contractions and no pain. If the efficacy of MS is better than PFMT, which has a success rate of approximately 30 %, it may be a reasonable option for patients with SUI who are not keen to undergo surgery. The results of our trial are expected to add essential confirmatory data regarding whether MS is effective for women with SUI.

Our protocol has some limitations. To maximally exclude any placebo effects, various considerations were taken when designing the sham MS. We used the same MS device, designed a coil that can be tilted to adjust the strength of contractions, and included only subjects who are naive to MS. Nevertheless, we think that our blinding methods may be unsuccessful in some patients. Selective refusal by participants in the present study may limit the generalizability of the study results to the wider public. Furthermore, when we first designed the trial, we specified a follow-up period of 6 months for logistical reasons. However, we intend to prolong our follow-up period to a minimum of 1 year, as recommended by guidelines [45]. Amendments have been made and submitted to our local ethics committee. Finally, we selected our sample size based on our primary outcome data analysis method (responder analysis: percentage of subjects who meet primary criterion of response). Our study may be underpowered for determination of statistical significance for the secondary outcome measures.

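### Comparing correct-guess rates between arms does not measure whether the guess depends on allocation, so it is the wrong contrast for judging blinding

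*Protocol article*

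**What the plan says.** The section on blinding and control for bias states the purpose: "To evaluate the effectiveness of blinding of study participants, each subject will be asked to answer the following question". The question asks which treatment the woman thinks she received. "The subject will have three possible answers": active, don't know, or sham. The analysis is then fixed in one sentence: participants' "ability to correctly identify treatment assignment at the end of the 8-week treatment will be analyzed and compared between the two treatment groups".

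Table 1 places the assessment at visit 16 (week 8), and the Discussion repeats the timing: "Subjects will also be assessed for effectiveness of blinding at the end of the 8-week treatments". No other comparison of the guesses is described. Under its limitations, the Discussion concedes that "we think that our blinding methods may be unsuccessful in some patients", without adding an analysis.

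**The concern.** Blinding holds when the guess is unrelated to the arm. The planned contrast compares a different quantity, the share of right answers. Because the right answer changes with the arm, two equal shares can mean heavy unblinding in both arms, and two very different shares can mean that everyone leaned toward the same guess.

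Both situations are conceivable here. The sham uses a tilted coil and lower intensity, with 136 kJ delivered over the eight weeks against 408 kJ for one full-intensity active session, so women in either arm might sense what they received. On the other hand, all participants are new to the treatment and all are told to expect a possible tingling, so a shared lean toward 'active' is also possible.

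What is at stake is interpretation. The primary outcome is a self-administered questionnaire, and readers will look to the guess data when judging whether a difference in response could reflect expectation.

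**Working it through.** **Inputs from the protocol article**
- Allocation (Randomization): "Subjects will be assigned in a 1:1 allocation to either the active or sham MS group".
- Size (Sample size calculation): "the enrollment goal is 120 subjects", so 120 / 2 = 60 per arm.
- Attrition (same section): "Allowing for a 25 % dropout rate", so 60 × 0.75 = 45 per arm answering.
- Guess rates: none are given. Every rate below is an assumption. The article states no figure for the blinding analysis, so there is none to reproduce.

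**Algebra**

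Let `a_act` and `a_sham` be the shares saying 'active' in the active and sham arms, and `s_sham` the share of the sham arm saying 'sham'.
- Planned contrast: D = `a_act` − `s_sham`.
- Dependence of the 'active' guess on arm: G = `a_act` − `a_sham`.

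If nobody answers 'don't know', `s_sham` = 1 − `a_sham`, so D = `a_act` + `a_sham` − 1. D then tracks how often 'active' is guessed overall, while G tracks whether the guess follows allocation. More generally:
- Equal unblinding means equal correct rates in the two arms, so D = 0 at any severity.
- Intact blinding means the same guess distribution in both arms, so D = P(says active) − P(says sham). This is zero only if the two guesses are equally common.

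Neither result depends on sample size.

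**Case 1: both arms unblinded, 85% correct in each, no 'don't know'**
- D = 0.85 − 0.85 = 0; p = 1.
- G = 0.85 − 0.15 = 0.70. The pooled share is 0.50 and the standard error is √(0.50 × 0.50 × 2/60) = 0.0913, so z = 0.70/0.0913 = 7.7.

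**Case 2: blinding intact, 70% say active and 30% say sham in both arms**
- G = 0.70 − 0.70 = 0.
- D = 0.70 − 0.30 = 0.40. At 60 per arm, z = 0.40/0.0913 = 4.38, p about 0.00001. At 45 per arm the standard error is √(0.50 × 0.50 × 2/45) = 0.1054, z = 3.79, p about 0.00015.

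**Case 2 with 'don't know' used: 60% active, 20% don't know, 20% sham in both arms**
- Correct rates are 60% and 20%, so D = 0.40. Fisher's exact p is 0.000014 at 60 per arm and 0.0002 at 45. The guess-by-arm comparison gives p = 1.

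**Case 3: unblinding in one arm only**
- All of the active arm say active; the sham arm divides 60% active, 40% sham. D = 1.00 − 0.40 = 0.60 and G = 1.00 − 0.60 = 0.40.
- A shared lean of 80% active, 20% sham in both arms gives the same D = 0.80 − 0.20 = 0.60, with G = 0.
- D responds to one-arm unblinding but cannot tell it from a shared lean.

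**Bang index (share correct minus share incorrect in an arm)**
- Case 1: 0.85 − 0.15 = +0.70 in both arms.
- Case 2: active arm 0.70 − 0.30 = +0.40; sham arm 0.30 − 0.70 = −0.40. With no 'don't know' answers, the standard error at 60 per arm is 2 × √(0.70 × 0.30/60) = 0.118, so the active-arm 95% interval is 0.40 ± 0.23, about 0.17 to 0.63. Read alone, this excludes zero although nothing is unblinded. The signs in the two arms have to be read together.

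**The case against.** The article states no test and no rule for declaring blinding successful or failed. A reader might infer that a non-significant difference would be taken as success; the text does not say so. It says that correct identification will be analyzed as well as compared, and any such report would show the rate in each arm, so 85% against 85% would be visible. This stands, and it limits the claim: the contrast can mislead, but the article does not commit to a misleading conclusion.

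The choice of blinding statistic is often left to an analysis plan, which is not shown. That would answer a complaint about missing detail. It does not remove this point, because the article does name a comparison, and correctness between arms is the only one it names.

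A reader might also infer that the planned contrast always points the wrong way. It does not: Case 3 shows that it can react to unblinding in one arm. Nor does the article support any particular lean toward 'active'; those rates are assumed.

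Finally, importance can be overstated. A guess made at the end of treatment is influenced by perceived benefit, so it is limited evidence on expectation however it is analyzed. The article describes appearance and noise as identical in the two arms, and the pad test and perineometry are done by assessors not told the allocation. All three answers are collected, so the better table can be made at any time. These points lower the weight of the finding without changing which contrast is appropriate.

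**Conclusion.** The point holds in a limited form. The comparison named in the article does not measure dependence of the guess on allocation. It is zero under equal unblinding of any degree, and it departs from zero under intact blinding whenever 'active' and 'sham' guesses differ in frequency. This is algebra and needs no assumption. The illustrated sizes rest on assumed guess rates: p = 1 for the planned contrast against z of about 7.7 for guess by arm when 85% are correct in both arms, and p of about 0.00001 (60 per arm) or 0.00015 (45 per arm) with no unblinding when 70% of both arms say active.

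A reader might go further and infer that blinding has failed, or that the primary result is compromised. The documents support neither. The conceded limitation refers to some patients only, and the blinding check does not enter the primary estimate or test. What is affected is how the blinding result can be read.

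**What to change.** Replace the sentence on correct identification with one that (a) tabulates the three answers (active, don't know, sham) by arm and (b) compares that guess distribution between arms.

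As a supplement, report the Bang index with its 95% confidence interval for both arms, and state that the two are interpreted jointly: values such as +0.4 and −0.4 indicate a shared lean, while +0.7 and +0.7 indicate unblinding. Add a caution that an end-of-treatment guess is influenced by perceived benefit. For the same reason, a responder comparison within guess categories should not be added as a check on blinding, since it would condition on a variable affected by the outcome.

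The question, the visit and the data stay as they are, and the primary test is unchanged. The cost is analysis wording, best settled before the guesses are tabulated against allocation.
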